### Inclusion/exclusion criteria

All subjects must meet all inclusion criteria and must not meet any of the exclusion criteria.

#### Inclusion criteria

1. Infertile women younger than 40 years old;

2. Pelvic endometriosis lesions confirmed by laparoscopy or laparotomy, which is described in detail in the surgical records and can be scored;

3. Meet the indications to receive IVF/ICSI treatment;

4. Normal blood FSH levels (FSH < 12 IU/L);

5. In line with the national family planning policy;

6. The patient signed the informed consent and was willing to complete the follow-up on time.

#### Exclusion criteria

1. Patient with alcoholism, tobacco addiction, or drug abuse habits;

2. Patient with any serious cardiovascular, lung, liver, or kidney diseases;

3. Patient with contraindications to pregnancy;

4. Patient with preimplantation genetic diagnosis (PGD) or preimplantation genetic screening (PGS);

5. Patient with other ovarian surgical history other than endometriosis surgery;

6. Patients with uterine fibroids (fibroids with a diameter larger than 3 cm or closely related to the endometrium);

7. Patients with hydrosalpinx;

8. Patients with adenomyosis;

9. Patients with untreated endometrial polyps;

10. Patients with intrauterine adhesions;

11. Pap smear test (ThinPrep cytologic test, TCT) indicating stage III/IV within 6 months;

12. Number of previous IVF/ICSI attempts ≥3;

13. Patients participating in any other clinical trials.

### Grouping method

Center controlled grouping will be performed. After entering the IVF/ICSI cycle and establishing medical records, the researchers at each center will screen for patients who meet the enrollment requirements according to the inclusion and exclusion criteria. Patients with endometriosis will be scored, and the degree of endometriosis (mild, moderate or severe) will be evaluated and recorded in a Microsoft Excel spreadsheet for each center. At the same time, the researchers at the center will be contacted, and the statisticians at the center will group the patients according to the number randomly generated by Excel or contact the central office.

### Blind method

The study is single-blinded; the doctor who prescribes the drug for ovulation induction will determine the ovulation induction regimen. Both physicians for Ovum pick up and embryo transfer, and embryologist handling embryos are blinded in this study.

## Method

All women who are confirmed to have endometriosis by laparotomy or laparoscopic surgery will visit the reproductive center and receive assisted pregnancy treatment. After the patients enter the IVF/ICSI cycle and establish medical records, the researchers at each center will screen patients who meet the enrollment requirements according to the inclusion and exclusion criteria. The patients will be fully informed about why they were enrolled in the study. If the patients are highly satisfied with the explanation about this research and decide to participate in the study after careful consideration, they will be asked to sign an informed consent form. Patients will understand they could withdraw voluntarily from this clinical study at any time, and the person in charge at each center will provide the patient with their contact phone number. If the patient decides to withdraw, it will be recorded as lost. See Fig. 1.

**Fig. 1 Fig1:**
[figure not shown]
Participant flow chart through the trial

### Research plan

#### The classic ultra-long-acting regimen—ultra-long-acting regimen with two injections

The patients will visit the hospital on menstrual day 2. If the vaginal B-scan ultrasonography does not find cysts and follicles > 10 mm, then 3.75 mg of long-acting GnRHa (Diphereline is the common choice) will be injected. The patient will attend a checkup 28 days after the injection to examine the B-scan ultrasonography+FSH, luteinizing hormone (LH), E2, and P. If ovarian endometriosis is found, then a B-scan ultrasound-guided aspiration biopsy of the cyst will be performed. An intraoperative aspiration of the cyst fluid will be obtained and saline will be used to repeatedly rinse the cyst cavity. At the same time, the second 3.75 mg of long-acting GnRHa will be injected. Twenty-eight to 30 days after the injection (to be adjusted slightly according to the diagnosis and treatment habit of the center or decided according to the patient’s condition), the patient will attend a checkup to examine the B-scan ultrasonography+FSH, LH, E2, and P to see whether they have achieved down-regulation criteria. The down-regulation criteria are E2 < 50 pg/ml, *P* < 0.8 ng/ml, LH < 3 mIU/ml, and endometrium thickness ≤ 5 mm. The researchers then determine the Gn initiation time according to follicle and hormone conditions. See Fig. 2.

**Fig. 2 Fig2:**
[figure not shown]
Normal GnRHa protocol

#### Early follicular phase long-acting regimen—Ultra-long-acting regimen with one injection

The patient will visit the hospital on menstrual day 2. If the vaginal B-scan ultrasonography does not find cysts and follicles > 10 mm, then 3.75 mg of long-acting GnRHa (Diphereline is the common choice) will be injected. The patient will attend a checkup 28 days after the injection. If ovarian endometriosis is found, then a B-scan ultrasound-guided aspiration biopsy of the cyst will be performed. An intraoperative aspiration of the cyst fluid will be obtained, and saline will be used to repeatedly rinse the cyst cavity. On the same day, B-scan ultrasonography+FSH, LH, E2, and P will be examined. Thirty to 40 days after the injection, patients are expected to reach down-regulation criteria. The down-regulation criteria are E2 < 50 pg/ml, *P* < 0.8 ng/ml, LH < 3 mIU/ml, and endometrium thickness ≤ 5 mm. Then, Gn will be started. See Fig. 3.

**Fig. 3 Fig3:**
[figure not shown]
Shorten GnRHa protocol

#### Gn starting dose

According to the subject’s age, BMI, antral follicle number, and medical history, the researchers at each center will give a recommendation on a random date, while the details will be decided after a reevaluation by the researchers on the start date, usually 112.5–150 IU. During ovulation induction, the Gn will be increased or decreased timely according to the number, size, and growth of follicles.

### Gn adjustment

The researchers will determine the increase and decrease in Gn based on the hormone status and follicular development, and human menopausal gonadotropin (HMG) will be added in a timely manner (Menotrophin will be used in all cases).

### Criteria for HCG injection

The criteria for HCG injection include the following: when the diameter of one primary follicle is ≥20 mm and the diameter of the other follicles is ≥18 mm, or the quantity of follicles with a diameter ≥ 14 mm accounts for more than 2/3 of the follicles. The trigger drug and HCG exposure time will be determined by the researchers according to the patient’s body weight, estrogen levels, and follicle condition. Ovidrel + HCG 2000 IU trigger will be given routinely.

### Egg retrieval

Eggs will be retrieved 36–37 h after HCG administration according to the routine procedure of each center.

### Embryo transfer

On the third and fifth days after the eggs are taken, 1–2 embryos or blastocysts will be transferred depending on the quantity and quality of the embryos.

### Luteal support

All women undergoing IVF-assisted pregnancy will start luteal support once the eggs are taken. They will be treated with Crinone (Switzerland, Merck-Serono) 400 mg/day, and Duphaston tablets (USA, Abbott) 20 mg/day until the early pregnancy test. If the test is positive, the administration of both drugs will be continued. Crinone will be stopped at 45 days after the transfer, while Duphaston will be stopped at 65 days after the transfer.

### Pregnancy test

Blood and urine HCG will be routinely measured 14 days after embryo transfer.

### Ultrasound test of early pregnancy

Thirty-five days after the embryo transfer, abdominal ultrasound will be used to determine the size of the gestational sac, fetal bud, and the primitive heart tube beat.

### Criteria for canceling embryo transfer

1. *P* > 3 ng/ml on the day of HCG administration;

2. Presence of uterine effusion on the day of transfer;

3. Moderate to severe ovarian hyperstimulation criteria are met on the day of transfer according to the OHSS grading criteria [8]:

### Study steps and observation parameters

#### Study steps

##### Visit 1

Screen for subjects based on inclusion/exclusion criteria;

Explain the study to the subjects and have the subjects sign the informed consent form;

Collect medical history and demographic information and perform routine physical examination (including height and weight) and pelvic examination;

Count antral follicles;

Baseline anti-Müllerian hormone (AMH), FSH, LH, E2, testosterone (T), P, and prolactin (PRL) levels in serum.

##### Visit 2 (down-regulation and ovarian stimulation)

Record the time to start the down-regulation treatment;

Record the serum FSH, LH, E2, and P levels after down-regulation but before giving Gn;

Record the number and size of antral follicles after down-regulation but before administration Gn;

Initiation dose: 112.5–150 IU, maximum dose 300 IU.

##### Visit 3 (Gn 6–7 days)

Record the serum LH, E2, and P levels for 7 days;

Record the size and number of follicles.

##### Visit 4 (the day HCG was administered)

HCG medication regimen and time: Once there is evidence to show that follicular development was mature; Ovidrel + HCG 2000 IU trigger will be given. If the patient has OHSS tendencies, we will refer to the diagnosis and treatment routine of our center to give Ovidrel or HCG (3000–4000 IU) to minimize the occurrence of serious complications.

Record the total amount of Gn and medication time;

Record the E2 level;

Record the number of follicles < 14 mm, 14–16 mm and > 16 mm;

If the cycle is canceled (if no HCG was given), the reason for stopping the treatment should be recorded in the case report form, and this visit will become the last visit for that subject.

##### Visit 5 (embryo transfer)

According to the assisted reproduction treatment plan of our center, egg retrieval, IVF/ICSI, embryo transfer, and luteal phase support will be performed.

The following data will be collected:

Gn category;

Gn dosage;

E2 and P levels;

The numbers of follicles ≥14 mm, ≥16 mm, and ≥ 18 mm;

The date the eggs were taken;

The number of eggs taken;

Oocyte insemination date;

ART method: IVF or ICSI;

Number of fertilized oocytes;

Number of 2PN eggs;

2PN cleavage rate;

Good-embryo rate;

The date of embryo transfer;

The number of transferred embryos;

The number of cryopreserved embryos;

The size of ovary;

Pelvic effusion volume;

If OHSS whole embryo freezing occurs, the OHSS level, whether the patient was hospitalized, the length of hospitalization and the outcome should be recorded;

If no embryo transfer was performed, the reason should be recorded in the case report form and this visit will become the last visit for that subject.

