In this study, we will use an RCT to compare the fresh embryo transfer rate, pregnancy rate, total Gn and other indicators during the ovulation induction application of the ultra-long-acting regimen with one dose or two doses of long-acting Triptorelin in patients with endometriosis, aiming to provide a safer and more effective ovulation induction regimen for patients with endometriosis.

Centers involved in the study:

1. Center for Reproductive Medicine, the First Affiliated Hospital of Zhengzhou University, Zhengzhou, China

2. Jiangxi Provincial Maternal and Child Health Hospital in Nanchang

3. Center for Reproductive Medicine, Third Affiliated Hospital of Zhengzhou University, Zhengzhou, China

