#### Secondary study endpoints

1. Estradiol (E2) level on the day of human chorionic gonadotrophin (HCG) administration

2. Progesterone (P) level on the day of HCG administration

3. The number of oocytes retrieved

4. Gn dosage

5. Gn duration

6. Metaphase II (MII) ratio (during ICSI injection) (%)

7. Two-pronuclei (2PN) ratio (%)

8. Embryos available for transfer

9. Ratio of fresh cycle to transfer cycle (%)

10. Incidence of moderate-to-severe ovarian hyperstimulation syndrome (OHSS) (%)

11. Implantation rate (%)

12. Early miscarriage rate

13. Ectopic pregnancy rate

14. Ongoing pregnancy rate

15. Live birth rate

16. Multiple pregnancy rate

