##### Visit 6 Biochemical pregnancy assessments

Fourteen days after embryo transfer, blood HCG will be tested. If the result is positive, then 5 weeks after the embryo transfer ultrasound examination will be conducted to evaluate the pregnancy. If the result is negative, this visit will become the last visit for that subject.

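### The moderate-to-severe OHSS endpoint has no time window, but the visit schedule lists OHSS only at Visit 5 and only when all embryos are frozen, so later cases have no listed place to be recorded

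*Protocol article*

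**What the plan says.** All references are to the protocol article.

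- **Secondary study endpoints, item 10:** "Incidence of moderate-to-severe ovarian hyperstimulation syndrome (OHSS", expressed as a percentage. It has no time window and no restriction to cancelled cycles. The Abstract also names it among the outcomes.
- **Criteria for canceling embryo transfer, item 3:** "Moderate to severe ovarian hyperstimulation criteria are met on the day of transfer according to the OHSS grading criteria". Items 1 and 2 cancel transfer for other reasons (progesterone on the HCG day, uterine effusion).
- **Visit 5, the OHSS item:** "If OHSS whole embryo freezing occurs, the OHSS level, whether the patient was hospitalized, the length of hospitalization and the outcome should be recorded". Ovarian size and "Pelvic effusion volume" are listed at the same visit without any condition.
- **Visit 5, no transfer:** "the reason should be recorded in the case report form and this visit will become the last visit for that subject".
- **Visit 6:** "Fourteen days after embryo transfer, blood HCG will be tested". A negative result ends participation.
- **Visits 7 to 9:** pregnancy ultrasound; pregnancy status and early miscarriage; live birth, late miscarriage, prematurity and newborn health. None lists OHSS.
- **Background, aim:** "aiming to provide a safer and more effective ovulation induction regimen for patients with endometriosis".

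**The concern.** An incidence with no window covers every case that follows stimulation, whenever it begins. The schedule collects the grade at one time point and under one condition, and that condition is a consequence of OHSS (freezing of all embryos) rather than OHSS itself. A woman who has a fresh transfer was free of moderate-to-severe OHSS that day by the cancellation rule, and no later visit lists an item that could change her status. If sites follow the schedule as written, she is counted as event-free whatever happens next.

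What is at stake is one secondary safety endpoint. A low recorded rate could be reported as low OHSS incidence when it is the rate of OHSS leading to a cancelled transfer. A comparison between arms would also cover early cases only, so a difference in later cases would go unseen.

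**Working it through.** **The plan's own figure.** The document's only computed figure is the sample size for clinical pregnancy. With rates 0.60 and 0.65, margin 0.05, one-sided alpha 0.05 and 90% power (unpooled):

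n = (1.645 + 1.282)² × (0.65×0.35 + 0.60×0.40) / (0.05 + 0.05)² ≈ 8.564 × 0.4675 / 0.01 ≈ 400.4, rounded up to 401 per arm.

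Adding 5% gives 401 × 1.05 = 421.05, taken as 421, and 2 × 421 = 842. This reproduces and does not bear on the point. The document gives no rate, timing or power for OHSS.

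**Following each woman through the schedule.**

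1. *Moderate-to-severe OHSS present on transfer day:* transfer is cancelled, so the freezing item should apply and the case is recorded.
2. *Fresh transfer, OHSS begins later:* Visits 6 to 9 list no OHSS item, so the case has no listed place.
3. *Transfer cancelled for another reason, OHSS begins after Visit 5:* Visit 5 was her last visit, so the case has no listed place.
4. *All embryos frozen for OHSS:* recorded. However, length of stay and outcome may not be known at Visit 5, which is also stated to be her last visit.

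The gap is therefore rows 2 and 3, and row 4 is an inconsistency to resolve. The unconditional ovarian size and effusion items help with grading at Visit 5 only.

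**Illustration of size, on assumed inputs.** Let L be the share of moderate-to-severe cases that begin after Visit 5. Then recorded rate = true rate × (1 − L), and missed cases = 401 × (p1 + p2) × L. Two-sided 5% power is Φ{[d − 1.96√(2p̄(1−p̄)/n)] / √[(p1q1 + p2q2)/n]}, with n = 401 and q = 1 − p. Assuming true rates of 5% and 2.5%, about 401 × 0.075 = 30 cases occur in all:

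| L | Recorded rates | Missed cases | Power |
|---|---|---|---|
| 0 | 5.0% v 2.5% | 0 | 46% |
| 20% | 4.0% v 2.0% | 6 | 38% |
| 40% | 3.0% v 1.5% | 12 | 30% |
| 60% | 2.0% v 1.0% | 18 | 21% |

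With L = 40%, assumed true rates of 3% v 1.5% take power from 30% to 20%, and 10% v 5% from 77% to 54%.

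**Can the direction be hidden?** Assume a 5% control rate, with early OHSS 30% lower and late OHSS 30% higher on one dose. The true one-dose rate is 5% × [0.7(1 − L) + 1.3L] = 5% × (0.7 + 0.6L), which exceeds 5% only if L is above 50%.

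- L = 20%: recorded 2.8% v 4.0%, true 4.1% v 5.0%.
- L = 40%: recorded 2.1% v 3.0%, true 4.7% v 5.0%.
- L = 60%: recorded 1.4% v 2.0%, true 5.3% v 5.0%.

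The record overstates the benefit in all three cases and reverses the direction only in the last.

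**The case against.** The strongest objection is that the visit lists are not a complete case report form. The MII ratio is endpoint 6, yet no visit lists a count of MII oocytes. Progesterone on the HCG day is endpoint 2 and a cancellation criterion, yet Visit 4 lists only E2 (Visit 5 lists E2 and P without naming a day). A full protocol may hold an adverse-event procedure that captures later OHSS, and the exact derivation of an endpoint may sit in an analysis plan that is not shown. This stands in part and lowers confidence. It does not remove the point, because the article is not merely silent: it sets an explicit condition for recording OHSS and explicit last visits, and both conflict with an incidence that has no window.

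Three stronger readings are tempting, and the document does not support them.

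- *A reader might infer that the freezing condition loses cases already present at Visit 5.* The cancellation rule should bring cases of the endpoint's grade into the record, so the loss is of later cases.
- *A reader might infer that women frozen for OHSS are lost.* They are the ones who are recorded. Asking for stay and outcome even implies completion after the visit, which sits badly with calling that visit the last.
- *A reader might take the number of women with a transfer as the size of the loss.* If 80–90% of 421 had one (assumed), that would be 337–379 per arm, but this counts women without a later listed OHSS item, not missed events.

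**Conclusion.** The point holds in limited form. Collected as listed, endpoint 10 is OHSS leading to freezing of all embryos. It can fall short of the incidence it names but cannot exceed it. The shortfall cannot be estimated, because the document gives neither an OHSS rate nor its timing; the figures above rest on assumed rates and late shares and only show what could follow. The conclusion assumes that some moderate-to-severe OHSS begins after Visit 5 and that sites collect what the schedule lists. The last-visit rule and the request for hospital stay and outcome must also be reconciled.

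A reader might go further and conclude that the trial cannot support its claim to a safer regimen. The document does not bear that out. The Background rests the case for fewer injections on low-estrogen side effects as well, and OHSS appears in neither the hypothesis nor the stated objectives. What cannot be supported is a statement about overall OHSS incidence. The matter is worth correcting, at moderate confidence, and leaves the primary analysis untouched.

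**What to change.** 1. Record OHSS occurrence, grade (by the grading reference already cited under the cancellation criteria) and onset date for every woman given Gn, whether or not embryos are frozen, at Visit 5 and at the existing Visits 6 and 7. Visit 7 applies only to women who continue after a positive HCG.
2. For women without a transfer, let the OHSS safety record be completed after Visit 5, including length of stay and outcome, and reword the last-visit rule to match.
3. Define endpoint 10 over that window with a stated denominator: all randomized or all stimulated women. Women whose cycle stops before HCG leave at Visit 4, so the text should say how they are counted.
4. If later collection is not possible, rename the endpoint *OHSS leading to cancelled transfer* and do not report it as overall incidence.

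The cost is a few form fields at visits already held, later completion of the record for women without transfer, and possibly a higher reported OHSS rate. These are changes to data collection only. Sample size and treatment are unaffected.

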##### Visit 6 Biochemical pregnancy assessments

Fourteen days after embryo transfer, blood HCG will be tested. If the result is positive, then 5 weeks after the embryo transfer ultrasound examination will be conducted to evaluate the pregnancy. If the result is negative, this visit will become the last visit for that subject.

##### Visit 7 Clinical pregnancy assessments

The number of gestational sacs, the number of gestational sacs with embryonic bud and embryonic heartbeat, and the pregnancy position will be assessed by ultrasound examination. If there is no clinical gestation, then this visit will be the last visit for that subject.

##### Visit 8 Evaluation of continuous pregnancy

Approximately 12 weeks after embryo transfer, the continuous pregnancy status will be followed-up, and the presence or absence of early miscarriage will be recorded.

##### Visit 9 Evaluation of live birth rate

Approximately 40 weeks after transfer, the live birth rate will be followed up, and the presence or absence of late miscarriage, premature birth, and the health of newborns will be recorded. This visit or follow-up will be the last visit.

### End of study

The study will be considered complete when all of the following conditions are met:

The ovarian stimulation cycle was canceled (if HCG was not given);

No eggs were obtained;

No transfer;

Confirmed pregnancy status.

### Data statistics

#### Sample size of participants

This study is a non-inferiority study; that is, it works well when the clinical pregnancy rate does not significantly differ between the two arms. A statistical expert calculated the trial’s sample size based on the existing average IVF cycle outcome across the three reproductive centers and the differences in the outcomes within the existing literature. A total of 401 women in each group will achieve 90% power to detect a non-inferiority marginal difference between group proportions of − 0.0500. The control group proportion is 0.6000. The treatment group proportion is assumed to be 0.5500 under the null hypothesis of inferiority. Power was computed for cases in which the actual treatment group proportion is 0.6500. The test statistic is the one-tailed Z-test (unpooled). The significance level of the test is targeted at 0.0500. The significance level actually achieved by this design is NA [12, 18]. Considering a dropout rate of 5%, we plan to recruit 842 women in total.

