### Main research objective

Clinical pregnancy rate is no worse than that of a control group.

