#### Statistical analysis

Statistics will be treated rigorously according to the following steps:

Step 1: Summary of research data

Baseline characteristics and pregnancy results will be summarized, such as number of participants, withdrawal rate. For continuous variables (such as age, FSH level, the number of Gn days, and total Gn dose), mean and standard error will be shown, if the distribution is asymmetric, then median and quartile will be determined. For categoricalvariables (such as clinical pregnancy outcomes), percentage of different groups will be displayed.

Step 2: Comparison between groups

Chi-square test, fisher’s exact test, Mann-Whitney U testor the Kruskal-Wallis test will be usedto determine whether differences in the results of two groups have statistical significance (*p* value < 0.05). Subgroup analysis will be performed according to different degrees of patient’s endometriosis. Endometriosis will be divided into mild degree (grades I and II) and severe degree (grades III and IV) due to the concern of false negatives and false positives.

Step 3: Multivariable analysis and sensitivity analysis

If the baseline data are not balanced between the two groups after randomization, we will adjust the unbalanced factors and perform a multivariable analysis. We will perform sensitivity analysis for loss of follow-up, missing data, which may bias experimental results.

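### Non-inferiority is defined as no significant difference between arms, so a one-dose regimen exactly on the 5-point margin would pass about 70% of the time instead of 5%

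*Protocol article*

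**What the plan says.** Three parts of the protocol article bear on how the primary question will be answered.

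- **Main research objective:** "Clinical pregnancy rate is no worse than that of a control group". The Aim section says the same of one dose against two.
- **Sample size of participants:** the study is called a non-inferiority study, and this is explained by adding that "it works well when the clinical pregnancy rate does not significantly differ between the two arms". The section then gives a non-inferiority calculation: "A total of 401 women in each group will achieve 90% power", with a margin of -0.05, a control rate of 0.60, a one-dose rate of 0.55 under the null and 0.65 for the power. It also states "The test statistic is the one-tailed Z-test (unpooled"), with a target level of 0.05.
- **Statistical analysis:** Step 1 names clinical pregnancy as an example of a categorical variable. Step 2 lists "Chi-square test, fisher’s exact test, Mann-Whitney U" and Kruskal-Wallis tests, to "determine whether differences in the results of two groups have statistical significance" at p < 0.05. It mentions no margin, no confidence limit and no one-sided test.

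**The concern.** A non-inferiority claim requires the data to rule out a loss as large as the margin. A non-significant test of equality does not do that, because it is compatible with no loss and also with a loss well beyond 5 points. The sentence in the sample-size section treats the two as the same thing, and Step 2 supplies the tests that would put that reading into practice. The margin appears only as an input to the sample size.

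The primary conclusion is at stake. A shorter regimen could be reported as no worse on data that fail the protocol's own 5-point criterion. The rule also favours imprecise data: the smaller the effective sample, the easier it is to pass. Taken literally, it has the opposite fault too, since a significant advantage for one dose is also a significant difference.

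**Working it through.** **Inputs**, all from Sample size of participants: 401 per arm, control rate 0.60, margin 0.05, one-dose rate 0.55 (null) and 0.65 (alternative), one-sided level 0.05, power 90%, 5% dropout, 842 recruited (421 per arm).

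**1. Reproduce the plan's figure.** With unpooled variance,

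n = (1.645 + 1.282)² × (0.60×0.40 + 0.65×0.35) / (0.05 + 0.05)² = 8.564 × 0.4675 / 0.01 = 400.4, rounded up to **401 per arm**.

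This matches, and so does 401 × 1.05 = 421. The sizing therefore rests on a margin-based test.

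**2. Chance of passing under the written rule at the margin (0.60 against 0.55).**

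- Standard error used by the chi-square: √(2×0.575×0.425/401) = 0.0349.
- Largest non-significant difference: 1.96 × 0.0349 = 0.068.
- True standard error: √((0.24 + 0.2475)/401) = 0.0349.
- Chance of not reaching significance: Φ((0.0684 − 0.05)/0.0349) = Φ(0.53) = 0.70.

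**3. Exact check.** Enumerating both binomial distributions, with the uncorrected chi-square at two-sided 0.05 and the unpooled Z-test against -0.05 at one-sided 0.05, gives for 401 per arm:

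| True one-dose rate (control 0.60) | Passes 'no significant difference' | Passes margin test |
|---|---|---|
| 0.55 (on the margin) | 70.2% | 5.05% |
| 0.52 | 37.2% | 0.6% |
| 0.50 (twice the margin) | 18.4% | 0.1% |
| 0.60 (equal) | 95.1% | 42.7% |
| 0.65 (as assumed for power) | 68.8% | 90.0% |

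In the last row, 31.1% of trials are significant in favour of one dose, which the literal wording does not count as success.

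**4. Sensitivity of the figure at the margin.**

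- 421 per arm: 69.3%.
- Continuity correction: 72.7% at 401 per arm and 71.6% at 421.
- One-sided 5% test for 'worse': about 59% at 401.
- 200 per arm, to show the direction of the effect: 83.0%.

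**5. What each rule demands of the data.** The written rule tolerates an observed deficit of up to about 6.8 points. The margin test needs an observed difference above -0.05 + 1.645 × √(0.48/401) = -0.05 + 0.057 = +0.007, so one dose must come out about 0.7 points ahead or better.

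Take as an illustration 241/401 (60.1%) on two doses and 214/401 (53.4%) on one dose, a difference of -6.7 points:

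- Chi-square: z = -0.0673/0.0350 = -1.92, p = 0.054, so not significant.
- 90% interval: -6.7 ± 1.645 × 3.49, that is -12.5 to -1.0 points.

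The written rule calls this a success. The interval extends far beyond -5 and excludes equality.

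**The case against.** The strongest reply is that the sentence about not significantly differing is loose English and not a decision rule. The same paragraph goes on to give a proper non-inferiority set-up: a margin, a null of inferiority and a one-tailed test. A charitable reader could take that Z-test as the primary analysis. Step 2 is a generic list that never names the primary endpoint, and a statistical analysis plan that is not shown may contain the margin test.

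Part of this stands. The margin is present in the document, so the fault is a wrong criterion that contradicts the sizing, and not an absent margin. The 70% holds if the sentence and Step 2 govern the primary conclusion. The protocol does not state the sidedness of p < 0.05, although a chi-square is two-sided in effect; a one-sided reading lowers the figure to about 59%. The remark that a significant advantage would count as failure is a literal reading, and it is secondary because the stated aim is only to be no worse.

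The main point is untouched. The only sentence that says what success means names the absence of a significant difference, and the only tests named for comparing the groups are tests of difference. This is stated text, not detail left to another document. An analysis plan with the right test would contradict it, so the text needs correcting either way.

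**Conclusion.** The concern holds. The protocol contains two incompatible criteria for its primary claim, and the one expressed as a criterion for success is invalid for non-inferiority. If it is followed, the false 'no worse' rate at the margin is about 70% (59% to 73% across readings of sidedness, continuity correction and 401 or 421 per arm), against the 5% designed for. It is still about 18% when the true loss is twice the margin.

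These figures assume the protocol's control rate of 0.60 and its planned sample size. Because the fault decides the primary conclusion, it must be corrected before the data are analysed.

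**What to change.** In Sample size of participants, delete the sentence that equates non-inferiority with not significantly differing. In Statistical analysis, add a primary-analysis rule such as:

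> Non-inferiority is concluded if the lower limit of the two-sided 90% confidence interval for the difference in clinical pregnancy rate (one dose minus two doses) lies above -5 percentage points. The chi-square p-value is not used for the primary conclusion.

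Keep the Step 2 tests for secondary outcomes. The 90% interval corresponds to the one-sided 0.05 already used, so the 401 per arm and the 90% power at 0.65 stay as stated.

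If two-sided 0.05 is intended, use the 95% interval and restate the power as about 83% (exact 83.5%). Keeping 90% power would then need (1.960 + 1.282)² × 0.4675 / 0.01 = 491.2, that is 492 per arm before dropout.

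The change is two sentences of wording, with no extra patients or data. It does make the trial harder to pass: if the two regimens are truly equal, the margin test succeeds in about 43% of trials at 401 per arm, against 95% under the present wording. That is a consequence of sizing on an assumed 5-point advantage for one dose, and it is no reason to keep the invalid rule.
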